### 4.4. Sample Size

Per Morin-Papunen et al., 2003, the most prominent serum metabolite testosterone decreased by 2.7 ± 0.3 to 2.0 ± 0.2 nmol/liter in patients receiving metformin (500 mg twice daily for 3 months or longer, then 1000 mg twice daily for 3 months or longer) [61]. By taking an alpha of 0.05% corrected by Bonferonni (0.005/44 (number of metabolites intended to analyze) = 0.001136) and a target power of 80% we would get an n = 7 patients [62]. However, this must be taken with a grain of salt as a very optimistic assumption for our purposes. We suggest that for not yet measured and reported effects on metabolites such as, e.g., androsterone, eticholanolone, dehydroepiandrosterone, epitestosterone effect sizes are much lower in the range of one-fourth of the above-mentioned testosterone. Therefore, the number needed to analyze will be around 45 patients. This estimate would be further supported by analyses by Baillargeon et al., 2004 [42], Chou et al., 2003 [46], Cibula et al., 2005 [47], Gambineri et al., 2006 [48], Ibanez et al., 2004 [49], Nestler et al., 1997 [41] and Tang et al., 2006 [50] analyzing effects of metformin mainly on androgen and estrogen markers. Furthermore, the proposed number of 45 would also potentially allow us to find an effect on steroid hormone profiles at lower dosages than described by Morin-Papunen [61]. Concerning the Autism questionnaire, it is to mention that an average score in students of 17.6 ± 6.4 was detected compared to healthy controls with an average score of 16.4 ± 6.3, yielding an alpha of 0.05% and a target power of 80% to a large sample size of 894 subjects [53]. When performing a comparison with students participating in the Math Olympiad scoring 24.5 ± 6.4 versus students with the already mentioned score of 17.6 ± 6.4, a sample size of 28 results [53]. These findings do not differ largely when it is stratified for sex, despite the fact that women tend to score lower [38]. To summarize, if there is a substantial effect of metformin, the proposed sample size of around 45 will be sufficient to detect differences.

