## 5. Statistical Analysis

Mean and SEM (standard error of mean) of all metabolites will be calculated pre-versus post intervention for the respective sub-samples distinguished by age and sex. To analyze the distribution patterns of the measured values of each metabolite Kolmogorov–Smirnov tests will be conducted. If normality distribution is present, the differences between pre-versus post intervention shall be analyzed with two-tailed dependent t-tests while correcting for multiple comparisons with Bonferroni correction. If the hypothesis of normal distribution must be rejected for metabolite concentrations pre-versus post intervention, Wilcoxon tests shall be conducted. If normal distribution is present, differences pre-versus post intervention will be further quantified with the calculation of effect sizes by Cohen with pooled standard deviation and 95% confidence intervals [63,64]. For metabolites not showing a normal distribution, effect sizes shall be calculated according to Pallant (2005) [65,66]. Correlation analysis (Pearson correlation coefficient) will be conducted to detect a potential relationship between cumulative metformin dosage (standardized for body weight and treatment duration] and steroid hormone concentrations, respectively, scores from the autism questionnaire. For female subjects before versus after menopause, analyses will be conducted separately. Potential differences will be compared with prior gained reference values from our lab [67]. As we do have a pool of healthy subjects, an individually pairwise matched design (twin matching) might be another possibility to reduce an age bias increasing the validity of the results [67].

Based on these preliminary analyses, structure equation modeling can be applied if indicated in order to combine findings from biochemical analysis and from questionnaires. All calculations will be performed with GraphPad Prism (GraphPad Software, Inc., La Jolla, CA, USA) and SPSS (Microsoft Inc., Redmond, WA, USA).

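### Holm's step-down correction would list at least as many changed metabolites as the planned single-step Bonferroni, at the same family-wise error

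*Protocol article*

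**What the plan says.** Section 5 of the protocol article prescribes, for normally distributed metabolites, "two-tailed dependent t-tests while correcting for multiple comparisons with Bonferroni correction". For the others, "Wilcoxon tests shall be conducted"; that sentence does not repeat the correction.

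Section 4.4 shows the form of the correction. It plans with an "alpha of 0.05% corrected by Bonferonni (0.005/44 (number of metabolites intended to analyze) = 0.001136", so one fixed threshold applies to each of 44 tests. For the full testosterone effect it states that with "a target power of 80% we would get an n = 7 patients". For the other metabolites it supposes that "effect sizes are much lower in the range of one-fourth of the above-mentioned testosterone", and arrives at about 45.

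The primary endpoint (Section 3.3.1) is change in the steroid profile, with no single primary metabolite. No step-down method is mentioned, and no reason is given for the single-step form. The 95% intervals for effect sizes in Section 5 are not described as adjusted for multiplicity.

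**The concern.** Because the endpoint is a profile, the useful result is a list of the metabolites that changed. The Discussion (Section 6) wants to read pathway and enzyme activity from it. Single-step Bonferroni keeps the threshold at 0.05/44 however many metabolites have already been declared changed. Once some null hypotheses have been rejected, fewer can still be falsely rejected, so that threshold is stricter than family-wise control requires. Holm's procedure uses this slack and needs no assumption beyond those of Bonferroni. At stake are true changes left off the list, not false ones put on it.

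**Working it through.** **Inputs.** From Section 4.4: 44 tests; 80% power; about 45 patients; "testosterone decreased by 2.7 ± 0.3 to 2.0 ± 0.2 nmol/liter"; one-fourth of that effect for other metabolites. From Section 5: two-sided paired tests. Assumed, because the protocol does not give them: the pre-post correlation, the correlation between metabolites, the number of metabolites that change, and an equal effect in each that does.

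**Step 1: the threshold.** 0.05/44 = 0.001136, which is the printed result. The printed fraction 0.005/44 would be 0.0001136, so 0.05/44 is the level actually used.

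**Step 2: the plan's own sample sizes.** The change is 2.7 − 2.0 = 0.7.
- Pooled SD: √((0.3² + 0.2²)/2) = 0.255, so d = 0.7/0.255 = 2.75, and one-fourth is 0.69. Exact paired-t power at 0.001136 needs n = 7 for the full effect and 41 for one-fourth.
- SD of the difference at an assumed pre-post correlation of 0.5: √(0.09 + 0.04 − 2 × 0.5 × 0.3 × 0.2) = √0.07 = 0.2646, so d = 2.646, and one-fourth is 0.661. This needs n = 8 and 44.

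The stated 7 and 45 are therefore reproduced to within a few patients, and the planning effect is d = 0.66 to 0.69. At n = 45, power per metabolite under Bonferroni is 82.0% for d = 0.661 and about 86% for d = 0.69.

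**Step 3: why Holm costs nothing in error control.** Order the p-values. After k rejections, the next one is compared with 0.05/(44 − k), stopping at the first failure. Suppose m₀ null hypotheses are true. When the first of them is falsely rejected, at most 44 − m₀ rejections have come before, so the threshold is at most 0.05/m₀. The chance that any of m₀ true nulls has a p-value that small is at most m₀ × 0.05/m₀ = 0.05, whatever the dependence. Each p-value must itself be valid, which Bonferroni also requires.

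**Step 4: how the threshold moves** (n = 45, d = 0.661, power of one test at that threshold).

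| Rejections so far | Threshold | Power |
|---|---|---|
| 0 | 0.05/44 = 0.001136 | 82.0% |
| 1 | 0.05/43 = 0.001163 | 82.2% |
| 10 | 0.05/34 = 0.00147 | 84.1% |
| 22 | 0.05/22 = 0.00227 | 87.5% |

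**Step 5: average power per truly changed metabolite**, by simulation of 44 paired t-tests (n = 45, d = 0.661, 20,000 runs per scenario), Bonferroni → Holm.

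| Changed of 44 | Metabolite correlation 0 | Metabolite correlation 0.5 |
|---|---|---|
| 1 | 81.6 → 81.6% | 82.1 → 82.1% |
| 5 | 82.1 → 82.8% | 81.9 → 82.5% |
| 10 | 82.0 → 83.6% | 82.3 → 83.6% |
| 22 | 82.0 → 86.3% | 82.1 → 85.6% |
| 33 | 81.9 → 89.8% | 82.0 → 88.4% |
| 44 | 82.0 → 97.7% | 81.9 → 93.3% |

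Simulated family-wise error under Holm was at most 0.049. The chance of at least one rejection was identical under the two methods in every scenario.

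With d = 0.66 to 0.69 and metabolite correlation 0.3 to 0.6, the gain is about 0.5 points with 5 changed, 1.5 to 2.5 with 13 to 15, 4 to 5 with 26, and 7 to 10 with 39.

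**Step 6: other sample sizes.** Section 3.6 expects around 100 patients after two years. At n = 100 and d = 0.661, Bonferroni power is already above 99.9%, so Holm adds less than 0.1 point. At n = 100 and d = 0.5 with 26 changed, power goes from 94.4% to 96.3%. For a stratum of 20 (assumed) at d = 0.661, it goes from 24.3% to 25.5% with 15 changed, and from 24.8% to 27.8% with 26.

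**The case against.** The strongest reply is that nothing here is wrong. Bonferroni is valid, Section 4.4 and Section 5 use it consistently, and Section 7.1 calls the study exploratory, where a simple conservative correction is defensible. The primary hypothesis in Section 2.1 is one global null. Holm's first step uses the same 0.001136, so the chance of rejecting that null does not change. All of this stands. It makes the point an efficiency improvement, not a correction of an error.

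A reader might infer that the plan expects most metabolites to change and that the gain is therefore large. The documents do not support that. The abstract speaks of a general alteration, but no count is given, and the earlier evidence cited in Sections 2 and 4.4 concerns mainly androgen and estrogen markers. Section 4.1 lists 13 androgen and 2 estrogen metabolites. If those 15 changed, the gain would be about 2 points. The chance of finding every changed metabolite moves more (with 26 changed and d = 0.6875, from 19% to 32% at correlation 0.3 and from 40% to 54% at 0.6), but the protocol does not set that as a goal.

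A reader might also want to exploit the correlation between metabolites with a sign-flip max-t procedure. That needs symmetric paired differences under the null, and it does not obviously fit a family that mixes t and Wilcoxon tests. The claim of no added assumption holds for Holm only.

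The last reply is that simultaneous confidence intervals matching Holm are less simple than Bonferroni intervals. That is true, but Section 5 does not describe its intervals as adjusted, so nothing stated in the plan is lost.

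**Conclusion.** The point holds as a small improvement that is almost free. For deciding which metabolites changed, Holm dominates single-step Bonferroni: same family-wise error, no rejection lost, some possibly gained. At 45 patients and the planned effect, the gain per changed metabolite runs from nothing (one changed) through about 2 points (13 to 15 changed) to 7 to 10 points (39 changed). It reaches about 4 points only if roughly half or more of the 44 change. It is near nil at 100 patients with the planned effect, and it does not lower the planned sample size.

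These figures assume equal effects across changed metabolites and equal correlation between metabolites. The lower effect, 0.66, also assumes a pre-post correlation of 0.5. The list in Section 4.1 names 39 metabolites, not 44. Dividing by 39 gives 83.0% power at n = 45 instead of 82.0%, so the conclusion does not depend on which count is right.

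**What to change.** In Section 5, replace *Bonferroni correction* by *Holm step-down correction at family-wise 0.05 over all metabolites, whichever test (t or Wilcoxon) is used for each*. The last clause also settles whether metabolites tested with Wilcoxon belong to the corrected family, which the present wording leaves open. Keep 0.05/44 in Section 4.4 as the conservative planning level.

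The cost is one phrase. Adjusted p-values follow from the sorted p-values by simple arithmetic, and no patient, sample or assay is added. If simultaneous intervals are wanted later, they will take more work than under Bonferroni.

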## 4. Data Collection Methods

### 4.1. Steroid Measurement Procedures

Analysis of urinary steroids will be conducted via gas chromatography–mass spectrometry. Urine samples shall be taken prior to treatment start and after 12 weeks of treatment (gold standard: 15 mL from a 24 h urine collection). Urine sample preparation comprises pre-extraction, enzymatic hydrolysis, extraction from the hydrolysis mixture, derivatization and gel filtration. The recovery standard will be prepared by adding 2.5 µg of medroxyprogesterone to 1.5 mL of urine. The sample will be extracted on a Sep-Pak C18 column (Waters Corp., Milford, MA, USA), dried, reconstituted in a 0.1 M acetate buffer, pH 4.6, and hydrolyzed with a powdered Helix pomatia enzyme (12.5 mg; Sigma Chemical Co., St. Louis, MI, USA) and 12.5 µL of β-glucuronidase/arylsulfatase liquid enzyme (Roche Diagnostics, Rotkreuz, Switzerland). The resulting free steroids will be extracted on a Sep-Pak C18 cartridge. A mixture of internal standards (2.5 µg each of 5α-androstane-3α, 17α-diol, stigmasterol, and cholesterol butyrate, and 0.15 µg of 3β5β-tetrahydroaldosterone) will be added to this extract, and the sample will be derivatized to form the methyloxime-trimethylsilylethers. Analyses will be performed on a Hewlett Packard gas chromatograph 6890 (Hewlett Packard, Palo Alto, CA, USA) with a mass selective detector 5973 by selective ion monitoring (SIM). One characteristic ion will be chosen for each compound measured. The derivatized samples will be analyzed during a temperature-programmed run (210–265 °C) over a 35 min period. The calibration standard consists of a steroid mixture containing known quantities of all the steroid metabolites to be measured. Responses and retention times will be recorded regularly. In each case, the ion peak will be quantified against the internal stigmasterol standard. All procedures will be performed as described several times by us and others [16,18,58,59,60].

The following metabolites shall be measured as described above [15,16]:

Androgen metabolites: Androsterone, Etiocholanolone, Androstenediol, 11-Oxoetiocholanolone, 11β-Hydroxyandrosterone, 11β-Hydroxyetiocholanolone, Dehydroepiandrosterone, 5-Androstene-3β,17β-diol, 16α-Hydroxydehydroepiandrosterone, 5-Androstene-3β,16α,17β-triol, 5-Pregnene-3β, 16α,17β-triol, Testosterone, 5α-Dihydrotestosterone

Estrogen metabolites: Estriol, 17b-Estradiol.

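### Bonferroni is stated only for the t-test branch, and a normality gate on raw concentrations sends skewed metabolites to Wilcoxon tests with no stated correction, at odds with a sample size built on alpha divided by 44

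*Protocol article*

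**What the plan says.** The primary endpoint (section 3.3.1) is change in the steroid profile over 12 weeks. No single metabolite is named as primary, so the primary hypothesis is tested metabolite by metabolite.

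Section 5 sets a two-stage rule:

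- **Gate:** "To analyze the distribution patterns of the measured values of each metabolite Kolmogorov–Smirnov tests will be conducted".
- **Normal:** differences are "analyzed with two-tailed dependent t-tests while correcting for multiple comparisons with Bonferroni correction".
- **Not normal:** "If the hypothesis of normal distribution must be rejected for metabolite concentrations pre-versus post intervention, Wilcoxon tests shall be conducted".

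The sentence on Wilcoxon tests mentions no correction, and no general multiplicity statement covers both branches.

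Section 4.4 derives the sample size with a corrected alpha: "By taking an alpha of 0.05% corrected by Bonferonni", worked out as "0.005/44 (number of metabolites intended to analyze) = 0.001136". There the divisor is the number of metabolites to be analysed, not the number that turn out normally distributed.

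**The concern.** Two features of the rule in section 5 interact.

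1. **The threshold depends on the branch.** Applied as written, the observed skewness of a metabolite decides whether it is judged at 0.00114 or at 0.05, a 44-fold difference. Skewed metabolites would then be the likeliest source of false positives on the primary endpoint.
2. **The gate looks at the wrong quantity.** A paired t-test needs approximately normal within-patient differences; it does not need normal pre or post values. Differences of two skewed, correlated measurements are usually much closer to symmetric than the measurements are. Gating on measured values therefore diverts metabolites for which the t-test was suitable, and it diverts them to the branch with no stated correction.

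At stake is error control for the primary hypothesis. A reported change in one or more metabolites could not be read as evidence at the level on which the trial was sized.

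**Working it through.** **Step 1: the plan's own threshold and n.** Inputs from section 4.4: testosterone 2.7 ± 0.3 falling to 2.0 ± 0.2, 44 metabolites, 80% power.

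- 0.05/44 = 0.001136, the figure the plan uses. The printed 0.005/44 would be 0.0001136, and the printed 0.05% divided by 44 would be 0.0000114. Only a 5% family-wise alpha gives the stated result.
- Pooled SD = sqrt((0.3² + 0.2²)/2) = 0.255; d = 0.7/0.255 = 2.746.
- A two-sided paired t-test at 0.001136 with 80% power needs n = 7, which matches the plan.
- At a quarter of the effect, d = 0.686 and n = 41; dividing by the Wilcoxon relative efficiency of 0.955 gives 43, against the stated 45 or so.

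The trial is thus sized on 0.05/44 for every metabolite.

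**Step 2: literal reading of section 5.** If k of 44 independent metabolites go to Wilcoxon at 0.05 and the rest to the t-test at 0.05/44, then

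FWER = 1 − (1 − 0.05)^k × (1 − 0.05/44)^(44 − k)

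| k | FWER |
|---|---|
| 0 | 4.9% |
| 10 | 42.4% |
| 20 | 65.1% |
| 30 | 78.9% |
| 44 | 89.5% |

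The documents do not give k. It depends on skewness, so it has to be assumed.

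**Step 3: simulating the gate.** Assumptions: 45 pairs, lognormal pre and post values, within-patient correlation 0.7, no effect, 44 metabolites. The gate is Kolmogorov-Smirnov (KS) at 5% on the pre or post values. A failure leads to Wilcoxon at 0.05, otherwise a paired t-test at 0.05/44. Plain KS uses ordinary p-values; the Lilliefors form allows for the estimated mean and SD. The plan does not say which is meant.

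For independent metabolites and plain KS, per-metabolite false-positive rates of 0.0091, 0.0222 and 0.0426 at log-SD 0.5, 0.7 and 1.0 give 1 − (1 − p)^44 = 33%, 63% and 85%. Repeat runs gave the ranges below.

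| Setting | Plain KS | Lilliefors |
|---|---|---|
| Independent, log-SD 0.5 | 27-33% | 87-90% |
| Independent, log-SD 0.7 | 63-66% | 87-90% |
| Independent, log-SD 1.0 | 85-88% | 87-90% |
| Inter-metabolite correlation 0.5, log-SD 0.5-1.0 | 25-60% | 59-65% |
| Inter-metabolite correlation 0.8, log-SD 0.5-1.0 | 16-36% | 30-38% |
| Mild skew, log-SD 0.3 | 5-7% | 64% (independent) |

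With 0.05/44 on both branches, theory gives 4.9% under independence and the simulations gave about 3-6%.

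**Step 4: what the gate adds.** With n = 45, the Lilliefors form and within-patient correlation 0.5 or 0.8:

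| Log-SD | Raw values fail | Differences fail | Only raw values fail |
|---|---|---|---|
| 0.3-0.5 | 48-88% | 10-34% | 41-61% |
| 0.8-1.0 | 99-100% | 76-95% | 5-24% |

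For mild to moderate skew, about half of metabolites would be diverted although their differences pass. For strong skew the differences mostly fail too. At log-SD 0.3-0.5 the per-metabolite false-positive rate was about 0.03-0.05 under the literal rule and about 0.001-0.002 with both branches corrected. Once both branches are corrected, the gate on its own adds little error.

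**The case against.** The best defence is that section 5 is silent on the Wilcoxon branch; it does not say that those tests go uncorrected. Section 4.4 divides alpha by all metabolites to be analysed, so one threshold throughout is the natural intention. This stands. A reader might infer that the investigators plan to test skewed metabolites at 0.05, or that the trial has a known family-wise error of some particular size. The documents support neither: they show two sections that do not agree.

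The size is also open to challenge, and rightly. Skewness, within-patient correlation, the form of the KS test and the correlation between metabolites are all assumed. Metabolites of one steroid pathway will not be independent, which lowers the inflation. Hence a range is given, with its near-nominal lower end.

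The study calls itself therapeutic exploratory (section 7.1), and two-stage normality testing is common. That lowers the stakes, but the plan does choose to control multiplicity, and the rule it prints does not do so.

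Two further readings are tempting. One is that raw concentrations without urine volume let a dilution change pass as a steroid effect. Section 4.1 names the "gold standard: 15 mL from a 24 h urine collection" and refers its procedures to cited work. How results are expressed is a detail that a condensed article may leave to the full protocol, so the text does not establish a fault. The other is that a log-ratio t-test is demonstrably more powerful here. That holds if the data are lognormal, which supports a preference but does not show an error.

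**Conclusion.** The point holds as a defect in a stated rule. Section 5 gives a correction for one branch only, section 4.4 assumes one for all 44 metabolites, and the gate is set on measured values instead of paired differences. The multiplicity gap is the main fault; the gate matters chiefly because it sends more metabolites into that gap.

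Followed literally, with 45 pairs and lognormal values at log-SD 0.5 to 1.0, family-wise error is about 30-90% for independent metabolites and about 16-65% at inter-metabolite correlation 0.5 to 0.8. With mild skew and plain KS it is 5-7%. With both branches corrected it is about 5%. The direction does not depend on these assumptions: any uncorrected Wilcoxon test raises the error above that of the corrected family. The size does depend on them.

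**What to change.** - State one family-wise procedure for all metabolites, whichever test is used. Bonferroni at 0.05 divided by the number of metabolites agrees with section 4.4. Holm controls the same error rate and never rejects less.
- In section 4.4, correct the printed alpha to the one actually used (0.05/44), and enumerate the family: section 4.1 lists 39 metabolites by count, not 44.
- Replace the gate with one paired test fixed in advance, for example a paired t-test on within-patient log(post/pre), with Wilcoxon as a sensitivity analysis. If a gate is kept, assess normality on the paired differences.

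The cost is revised wording, results reported as ratios, and a stated substitution rule for values below detection. Correcting the Wilcoxon branch has one consequence: the smallest exact two-sided p-value is 2/2^n, which is 0.00195 at n = 10 and 0.00098 at n = 11. Below 11 patients a corrected Wilcoxon test can never reach 0.00114. This affects the first rough analysis in 10 patients (section 3.6) and small subgroups. No patients had been included at submission (section 7.2), so at that stage the change could be made without reference to any data.

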### 2.2. Secondary Research Hypothesis

As a hypothesis with potential falsification, it shall be stated that a newly administered standard therapy with metformin has no influence on social behavior in subjects having an indication for metformin [19,51].

There is no statistical correlation between steroid hormone levels and social behavioral changes [51].

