#### 3.3.2. Secondary Research Endpoint

Changes in social behavior measured by the Autism-Spectrum Quotient AQ (see below) prior to metformin treatment start and after 12 weeks of treatment.

Correlation between steroid hormone profiles and social behavioral changes.

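### The dose correlations in Section 5 are worded as unadjusted levels although the endpoints are within-patient changes, and the secondary steroid–AQ correlation has no committed analysis

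*Protocol article*

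**What the plan says.** Protocol article, Section 5 (Statistical Analysis) names one correlation analysis: Pearson coefficients for a "potential relationship between cumulative metformin dosage (standardized for body weight and treatment duration] and steroid hormone concentrations, respectively, scores from the autism questionnaire". It states no time point, no change score and no covariate for them. Elsewhere the same section describes the metabolites "for the respective sub-samples distinguished by age and sex", and directly after the correlation sentence it says that women before and after menopause are analysed separately.

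The endpoints in Sections 3.3.1 and 3.3.2 are changes from before treatment to 12 weeks. Section 3.3.2 adds a further secondary endpoint: "Correlation between steroid hormone profiles and social behavioral changes". Section 2.2 gives its null hypothesis as "There is no statistical correlation between steroid hormone levels and social behavioral changes", and Section 3.2.2 repeats it as an objective. In Section 5 the only step that joins steroids to the questionnaire is that "structure equation modeling can be applied if indicated in order to combine findings from biochemical analysis and from questionnaires".

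The protocol is aware of sex and baseline differences. On the Autism-Spectrum Quotient (AQ), Section 4.4 says that its findings hold across sex "despite the fact that women tend to score lower". The Discussion lists sex and baseline hormone level, menopausal status in particular, among the factors that may alter effects.

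**The concern.** Steroid levels and AQ scores differ between patients for reasons unrelated to metformin, sex and menopausal status among them. Dose is not randomised: Section 3.5 leaves it to the treating physician. Dividing it by body weight ties it to body size, and so to sex. An unadjusted coefficient of dose per kg against a level can therefore pick up a difference between men and women and present it as a dose effect. The before-and-after design gives partial protection, but only if the analysis uses changes or adjusts for baseline.

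The steroid–behaviour link is the mechanistic result that the Discussion hopes to build on. If the test is chosen after the data are seen, including which variables enter as levels and which as changes, a positive result will be hard to interpret.

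**Working it through.** **1. Declared against planned**

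| Item | Steroid variable | AQ variable | Analysis in Section 5 |
|---|---|---|---|
| Dose correlation (Section 5) | concentrations | scores | Pearson, no adjustment stated |
| Secondary hypothesis (2.2) | levels | changes | none committed |
| Secondary endpoint (3.3.2) | profiles | changes | none committed |
| Aim in the Discussion (6) | change | change | none committed |

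The only named correlation has dose as one of its variables, so it cannot serve the last three rows.

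**2. Size of the possible dose artefact.** The protocol gives no sample size or power for any correlation, so there is no figure to reproduce.

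Inputs from the protocol: about 45 patients (4.4) or about 100 (3.6), slightly more men than women (3.6), doses from 500 mg to 3 g (3.5).

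Assumed inputs, not in the protocol: 55% men; mean weight 90 kg in men and 75 kg in women, SD 12; the same doses in both sexes, equally likely in 500 mg steps; log steroid level 0.8 higher in men, within-sex SD 0.5; no dose effect; both sexes in one coefficient.

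Dose per kg and level are then linked only through sex, so r = r(dose/kg, sex) × r(level, sex).

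- Mean dose 1750 mg; SD = 500 × √(35/12) = 854; squared coefficient of variation 0.238.
- Mean dose/kg ≈ (1750/weight)(1 + CV²): men 19.44 × 1.018 = 19.8; women 23.33 × 1.026 = 23.9; difference 4.1.
- Within-sex SD: men 19.8 × √(0.238 + 0.018) = 10.0; women 23.9 × √(0.238 + 0.026) = 12.3. Overall SD = √(0.55 × 10.0² + 0.45 × 12.3² + 0.2475 × 4.1²) ≈ 11.3.
- r(dose/kg, sex) = 4.1 × √0.2475 / 11.3 = 0.18 in size.
- r(level, sex) = 0.8 × √0.2475 / √(0.5² + 0.2475 × 0.8²) = 0.398/0.639 = 0.62.
- Induced r ≈ −0.11 (negative because lighter patients receive more per kg).
- Fisher z with 45 patients: 0.112 × √42 = 0.73, so P(significant) = P(Z > 1.23) + P(Z < −2.69) ≈ 11%. With 100 patients: 0.112 × √97 = 1.11, giving about 20%.

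Simulation agrees and gives the range:

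| Doses | Sex difference, log | Within-sex SD | n=45 | n=100 |
|---|---|---|---|---|
| 500–3000 mg | 0.8 | 0.5 | 11% | 20% |
| 500–3000 mg | 0.8 | 0.8 | 8% | 12% |
| 500–3000 mg | 0.4 | 0.5 | 7% | 9% |
| 1000–2000 mg | 0.8 | 0.5 | 21% | 41% |

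A second set of runs (sex difference 0.8, within-sex SD 0.5–0.7, two dose distributions, pre-post correlation 0.7) gave 9–20% and 18–42%. With log post minus log pre as the outcome, the stable sex difference cancels and the rate is 5–6%.

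**3. Cost in power.** With equal pre and post SDs, dose independent of baseline and pre-post correlation ρ, corr(dose, post level) = corr(dose, change) × √(2(1 − ρ)). At ρ = 0.8, a dose–change correlation of 0.30 appears as 0.30 × √0.4 = 0.19, and power with 45 patients at 5% falls from about 52% to 24%. At ρ = 0.5 there is no loss, and below 0.5 the level does better.

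**4. Multiplicity for the steroid–AQ test.** Section 4.1 lists 13 + 2 + 4 + 1 + 6 + 5 + 8 = 39 metabolites (Section 4.4 counts 44). Critical |r| = t/√(n − 2 + t²). With 45 patients it is 0.29 at 5% and 0.47 at 0.05/39. One uncorrected test per listed metabolite, all null, would give 39 × 0.05 ≈ 2 false positives on average.

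**The case against.** The protocol does not say that the sexes are pooled. It describes metabolites by age and sex and separates women by menopausal status. If that separation extends to the correlations and men form their own group, the artefact in step 2 largely disappears. This objection stands: pooling is something a reader might infer, and the text supports only that no stratification or adjustment of the correlations is stated.

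The dose sentence may simply be loose. The endpoints are changes, and an article may leave the exact variable to a fuller document. That softens the point but does not remove it, because the sentence as printed names concentrations and scores. The dose correlations are also not endpoints: Section 3.5 presents them as potential analyses, and Section 7.1 calls the study exploratory. This is a reason to label them so.

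A reader might infer that the steroid–AQ question gets no answer at all, or that some 80 uncorrected correlations are planned. Neither holds. The optional structural model could give an answer, the endpoint itself calls for a correlation, and an analysis that is not committed cannot be counted as a batch of uncorrected tests.

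Nor do changes remove all confounding. They cancel only stable level differences. If the response to metformin differs by sex, dose per kg against change is still confounded unless sex is in the model.

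**Conclusion.** The point holds in two parts.

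First, the dose correlations as printed use levels without stated adjustment, which leaves them open to between-patient confounding. If men and women share one coefficient, the false-positive rate is about 7–21% with 45 patients and 9–42% with 100, against 5–6% for changes. These figures rest on assumed body weights, dose spread and hormone differences. They span the scenarios run and are not bounds: a narrower dose spread or a larger sex difference raises them, and the reverse brings them towards 5%.

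Second, a declared secondary hypothesis, objective and endpoint has no committed test, and its variables are described inconsistently between Section 2.2 and the Discussion. This part needs no assumption. It is a conflict within the article, which does specify tests, a correction, effect sizes and a different correlation.

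The primary pre-post comparison is not affected.

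**What to change.** - **Dose analyses:** in Section 5, regress the within-patient change (log post/pre steroid; AQ post minus pre), or the post value, on standardised dose, with baseline value and sex/menopausal status as covariates, and age if degrees of freedom allow. Label these analyses exploratory.
- **Steroid–AQ endpoint:** name the test as change in log steroid against change in AQ, with the same adjustment and a stated multiplicity correction across the metabolites. Align the hypothesis in Section 2.2 with it.
- **Structural equation model:** label it exploratory.

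The cost is small. No new patients or visits are needed, and the variables are already collected or required for the planned dose standardisation. With 45 patients, an intercept, dose, baseline and three sex/menopause groups use 1 + 1 + 1 + 2 = 5 parameters and leave 40 residual degrees of freedom. If raw change is used without baseline adjustment, some precision is lost where the pre-post correlation is below 0.5; including baseline avoids this.
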